**Hematologic toxicity**

The ANC should be ≥ 1500/μL and the platelet count should be ≥ 100,000/μL before starting each cycle. In order to provide sufficient time for recovery, the treatment can be delayed for up to 9 weeks. After 2 dose reductions or treatment delays exceeding 9 weeks due to toxicity, treatment with etoposide and/or carboplatin was discontinued unless the investigator believed that patients could benefit from continued treatment. Growth factor therapy may be provided as per the American Society of Clinical Oncology (ASCO) and NCCN guidelines (Smith et al. 2006; NCCN 2015). At the beginning of subsequent cycles after recovery, the dose should be modified based on the PLT and ANC nadirs of the last cycle (refer to Table 4). Subjects who require dose modification due to both ANC and PLT should receive a lower dose.

**Table 4. Chemotherapy Dose Modification due to Hematologic Toxicity**

| **Toxicity**^a^ | **Carboplatin Dose** |
| --- | --- |
| ANC < 500/μL and PLT ≥ 50,000/μL | 75% of previous dose^b^ |
| PLT < 25,000/μL, ANC not considered | 75% of previous dose^b^ |
| PLT < 50,000/μL with Grade ≥ 2 hemorrhage, ANC not considered | 50% of previous dose^b^ |
| ANC < 1000/μL with fever ≥ 38.5 °C | 75% of previous dose^b^ |

a: Nadir of the last treatment cycle. b: The calculated dose before dose administration of each cycle.

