# DOSE AJUSTMENT AND DISCONTINUATION OF ADMINISTRATION

## General Rules for Dose Adjustment

- Reasons for dose adjustments or delays in administration, measures taken, and results should be documented in the subject's medical record and electronic case report form (CRF).
- If concomitant symptoms were present at baseline, it was the investigator to decide whether the dose would be adjusted according to the level of change in the adverse effect. For example, a subject with a Grade 1 "weakness" status at baseline and a Grade 2 "weakness" status during the study treatment period may be considered a "weakness" condition. The dose should be adjusted for grade 1 toxicity.
- In the event that several adverse reactions of different grades or severity occur simultaneously, dose adjustments will be based on the highest grade observed.
- If a dose adjustment is required solely due to an abnormal laboratory hematology test, the dose will be adjusted based on the hematology test prior to the start of the treatment cycle.
- The current dose will be continued without dose adjustment or suspension of treatment when, in the evaluation of the investigator, the adverse reaction is unlikely to progress further to a serious or life-threatening event.
- If the toxicity is caused by another medication, no dosage adjustment of the other medication is necessary.
- Permanent discontinuation of one therapeutic agent prior to the onset of PD will not affect the continued use of other therapeutic agents.
- If one of the therapeutic medications is suspended due to an adverse reaction, but not all of the medications, the treatment is still counted as one treatment cycle.

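### Table 4 states no carboplatin reduction for a platelet band lying between two that have one, and Sections 9.1 and 9.4 base the adjustment on different blood tests

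*Protocol*

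**What the plan says.** Table 4 in Section 9.4 of the protocol has four rows, each giving carboplatin as a percentage of the previous dose:

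- "ANC < 500/μL and PLT ≥ 50,000/μL": 75%
- "PLT < 25,000/μL, ANC not considered": 75%
- "PLT < 50,000/μL with Grade ≥ 2 hemorrhage, ANC not considered": 50%
- "ANC < 1000/μL with fever ≥ 38.5 °C": 75%

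Two places in Section 9.4 say which blood count is meant. The text on hematologic toxicity says that "the dose should be modified based on the PLT and ANC nadirs of the last cycle", and the first table footnote reads "a: Nadir of the last treatment cycle". The same text sets the condition for starting treatment: "The ANC should be ≥ 1500/μL and the platelet count should be ≥ 100,000/μL before starting each cycle".

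Section 9.1, which gives general rules for all study drugs, covers adjustments needed only because of abnormal blood counts. For these, "the dose will be adjusted based on the hematology test prior to the start of the treatment cycle".

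The opening of Section 9.4 presents the tables as guidance and lets chemotherapy doses follow the product labelling and local practice. It also bars a return to the full original dose after a reduction, and it makes two reductions part of the rule for stopping chemotherapy.

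**The concern.** There are two separate inconsistencies.

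First, as platelets fall at a fixed ANC below 500/μL, the table reduces the dose, then states no reduction, then reduces it again. A patient in the middle band has worse platelets than one for whom a reduction is printed, yet no row applies. Seeing this takes no clinical judgment, because the table departs from its own ordering.

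Second, the protocol names two different tests as the basis for the same kind of adjustment. Under one of them, part of Table 4 cannot operate.

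Safety is the primary endpoint (Section 2.1) of a single-arm study of 36 subjects (Section 4). Section 8 plans 2 induction plus 2 to 4 combination cycles with carboplatin, so 4 to 6 in all. The adjustment rules can therefore matter at 3 to 5 cycle starts per patient who completes them. Whether a reduction is triggered carries forward, because reductions are not fully reversed and count toward stopping chemotherapy. If sites fill the gap or settle the conflict differently, exposure and adverse event rates could differ for reasons unrelated to the regimen.

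**Working it through.** The protocol states no figure to reproduce. The check applies the table's logic as printed.

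**Step 1: Table 4 at a nadir ANC of 400/μL.** The inputs are the four rows above. Where several rows apply, the lowest dose is taken.

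| Nadir platelets (/μL) | No Grade ≥ 2 hemorrhage, no fever ≥ 38.5 °C | Fever only | Hemorrhage (with or without fever) |
| --- | --- | --- | --- |
| 80,000 | 75% | 75% | 75% |
| 50,000 | 75% | 75% | 75% |
| 49,999 | no row | 75% | 50% |
| 40,000 | no row | 75% | 50% |
| 25,000 | no row | 75% | 50% |
| 24,999 | 75% | 75% | 50% |
| 20,000 | 75% | 75% | 50% |

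The first row of Table 4 fails in the middle band because platelets are under 50,000/μL. The second fails because they are not under 25,000/μL. The third and fourth fail because their clinical sign is absent.

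**Step 2: is this the only such place?** The table was evaluated on a grid of ANC 400 to 1500/μL by platelets 20,000 to 100,000/μL, with and without each clinical sign. A cell was flagged if a patient with equal or better counts received a larger reduction. The only cells flagged had ANC 400 or 499/μL, platelets 25,000, 40,000 or 49,999/μL, and neither sign. The gap is therefore confined to ANC below 500/μL with platelets of 25,000 to 49,999/μL, without Grade ≥ 2 hemorrhage and without fever ≥ 38.5 °C.

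**Step 3: does other text close the gap?** Section 9.4 says that patients needing modification for both counts should have a lower dose. It gives no percentage, and in this band neither a count-only ANC row nor a count-only platelet row is met. Table 5 has a catch-all row, but it concerns non-hematologic toxicity only.

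**Step 4: size for one patient.** Table 4 works on the previous dose. For a patient with no earlier reduction, 75% is 5 × 0.75 = AUC 3.75. In the uncovered band no change from AUC 5 is stated. After an earlier reduction the figures differ.

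**Step 5: which blood test?**

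| Place | Test that governs |
| --- | --- |
| Section 9.1 | test before the start of the cycle |
| Section 9.4, hematologic toxicity text | nadir of the last cycle |
| Table 4, first footnote | nadir of the last cycle |

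No order of precedence is stated. A patient allowed to start a cycle has ANC ≥ 1500/μL and platelets ≥ 100,000/μL. The first row of Table 4 needs ANC below 500/μL, and the second needs platelets below 25,000/μL. Neither can be met by a pre-cycle test that permits the cycle to start. Both can be met by a nadir. Section 9.1 reaches only adjustments made solely for blood counts, so the direct conflict covers these two count-only rows.

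**The case against.** The strongest reply is that Section 9.4 is not a rigid algorithm. Doses may follow the product labelling and local practice, so an investigator may reduce the dose in the uncovered band. The next cycle must also wait for recovery of both counts, delay of up to 9 weeks is allowed, and growth factor support is available. The sentence on toxicity in both counts points toward less drug, not more. On the blood test, Section 9.1 is general while Section 9.4 is specific to chemotherapy, and anyone using Table 4 meets the nadir instruction in both the text and the footnote.

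Much of this stands as a limit on the practical effect. It does not put a row where none is printed, and the protocol never says that the specific section overrides the general one.

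Three stronger readings are tempting, and the documents do not support them:

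- **The uncovered patient must receive full dose.** The table is silent for that band, and Section 9.4 leaves room to adjust. What can be said is that no reduction is tabulated.
- **No row of Table 4 could ever apply under Section 9.1.** That section concerns adjustments made solely for abnormal counts. The hemorrhage and fever rows add a clinical sign and fall outside it.
- **The gap raises the rate of Grade 3 to 4 hematologic toxicity.** Neither the number of patients in the band nor any effect on event rates is given. An effect is possible but not shown.

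**Conclusion.** The point holds in two limited parts.

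Table 4 is inconsistent with its own ordering in one band: nadir ANC below 500/μL, platelets 25,000 to 49,999/μL, no Grade ≥ 2 hemorrhage and no fever ≥ 38.5 °C. Section 9.1 also conflicts with Section 9.4 and the Table 4 footnote on the governing test. If the pre-cycle test governs, both count-only rows (two of the four) are inoperative.

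This rests on reading the rows literally and on the cycle-start thresholds being observed. The consequence for the safety endpoint cannot be sized from the protocol; it is a risk of uneven application between sites. The rule misfires when followed as written, so it should be amended, although the freedom to adjust doses makes it less than critical.

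**What to change.** Reconcile Section 9.1 with the hematologic toxicity text of Section 9.4 and the Table 4 footnote, so that the protocol names one governing blood test or states which section takes precedence. The clinical team must also address the uncovered ANC and platelet band in Table 4. Which test and which dose are right is for the clinical team, and none is proposed here.

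The cost is an amendment to the wording and the table. Sample size, endpoints and analysis are unaffected.

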**Non-hematologic toxicity**

Treatment should be delayed (up to 9 weeks) if any non-hematologic toxicity occurs until the value returns to baseline or below baseline (or Grade ≤ 1 if the subject has no toxicities at baseline). At the beginning of the subsequent cycles, the dose should be reduced based on the non-hematologic toxicity observed from the last cycle. Table 5 provides the dose modification recommendations for non-hematologic toxicity.

**Table 5. Dose Modification or Treatment Discontinuation due to Non-Hematologic Toxicity**

| **Toxicity** | **Modified Carboplatin Dose (by % of Previous Dose)**^a^ | |
| --- | --- | --- |
| Diarrhea | Grade 3 or 4^b^ | 75% |
| Nausea/Vomiting^C^ | Grade 3 or 4 | 75% |
| Neurotoxicity | Grade 2 | 75% |
| Grade 3 or 4 | 50% or permanent discontinuation |  |
| AST, ALT, or Bilirubin  Increased | Grade 3 | 75% |
| Grade 4 | Discontinuation |  |
| Others | Grade 3 or 4 | 75% |

a The carboplatin dose can be modified by a specific percentage of the original AUC if deemed appropriate by the investigator. Previous dose: The calculated dose before dose administration of each cycle.
b Antidiarrheal agents are used for Grade 3-4 diarrhea or for any grade of diarrhea that requires hospitalization.
c Even when antiemetic therapy has been given.

Diarrhea should be treated with appropriate antidiarrheal agents. Nausea and/or vomiting should be treated with appropriate anti-emetics. If Grade 3 or 4 nausea/vomiting occurs, anti-emetics should be used and the dose should be reduced by 25% in the next cycle. The original dose should be resumed as soon as the subject is able to tolerate. If Grade 3 or 4 neurotoxicity occurs,chemotherapy should continue at 50% of the previous dose after improvement, or immediately be discontinued (based on the investigator's judgment).

**Table 6. Dose Modifications of Etoposide for Subjects with Renal Impairment.**

| **Creatinine Clearance (mL/min)** | **Etoposide Dose** |
| --- | --- |
| > 50 | 100% |
| 15-50 | 75% of previous dose^a^ |

a: The calculated dose before dose administration of each cycle.

# CONCOMITANT THERAPY

## Hematologic Support

Colony-stimulating factor (G-CSF or GM-CSF) or erythropoietin may be used prophylactically during treatment to prevent possible adverse events such as neutropenia.

## Treatment of Symptoms of Non-Hematologic Toxicity

Supportive therapies such as antiemetics, antibiotics, pain medications, blood pressure medications, and blood products may be used. Rinses can be used to treat or prevent stomatitis.

Unconventional therapy treatments (e.g., herbs or acupuncture) and vitamins/minerals may be used if the investigator believes there is no effect on the study's endpoints. Patients may receive bisphosphonates for bone metastases during treatment. If painful bone metastatic lesions are not effectively controlled by systemic therapy or local analgesia, small-area (radiotherapy area must be <5% bone marrow area) irradiation with palliative radiotherapy is permitted. Clinical co-morbidities and the presence of various types of AE should be actively treated and managed. All drugs used in combination should be recorded in the case report form (CRF) in strict accordance with GCP.

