# WITHDRAWAL CRITERIA

- Subjects withdrew informed consent.
- Progression of the disease on imaging.
- Those who cannot tolerate toxicity.
- Subjects missed visits or had positive blood HCG;
- Other situations where the investigator felt it necessary to withdraw from the study.

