# TRETAMENT REGIMEN AND DOSAGE

1. **Induction treatment stage: chemotherapy induction 2 cycles, q3w**

- Etoposide: 100 mg/m2 IV Day 1-3;
- Carboplatin: AUC 5 mg/mL/min IV Day 1

1. **Combination treatment stage: chemotherapy + immunotherapy + antivascular therapy 2-4 cycles, q3w**

- Etoposide: 100 mg/m2 IV Day 1-3
- Carboplatin: AUC 5 mg/mL/min IV Day 1
- Camrelizumab: 200 mg IV Day 1
- Apatinib: 250 mg PO QD

1. **Maintenance treatment stage: immunotherapy + antivascular therapy, q3w**

- Camrelizumab: 200mg IV Day 1
- Apatinib: 250mg PO QD

The treatment was administered in 3-week cycles until PD, intolerable toxicity, death, patient withdrawal of information, or discontinuation in the evaluation of the investigator.

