## Other Anti-tumor/Cancer or Investigational Drugs

Subjects are prohibited from receiving the following treatments during the treatment period of this study:

- Systemic chemotherapy and biologic therapy (including antitumor agents with immunomodulatory effects, including but not limited to, e.g., interferon, interleukin-2, thymosin, immune cell therapy, etc.).
- Immunotherapy not specified in this protocol.
- Drugs other than those specified in this study, including proprietary Chinese medicines with clear antitumor indications.
- Radiation therapy (Note: Sponsor may approve and allow radiation therapy to symptomatic isolated lesions or to the brain as long as it is not a lung or target lesion.).
- Live vaccines, including, but not limited to, the following: measles, mumps, rubella, varicella, yellow fever, rabies, BCG, and typhoid (oral) vaccines, within 28 days prior to the first dose of study medication of the study treatment and during participation in the study. Inactivated viral vaccines for seasonal influenza, administered by injection, are permitted; however, live attenuated influenza vaccines administered intranasally are not permitted.
- Corticosteroids, Inhaled steroids allowed for use in the treatment of asthma or chronic obstructive pulmonary disease (COPD) as part of stationary therapy. Corticosteroids for the management of potential irAE are allowed. Physiologic doses of corticosteroids are allowed. Allow prophylactic corticosteroids to avoid allergic reactions (e.g., intravenous contrast media).

Subjects requiring any of the above treatments, as assessed by the investigator, should be excluded from the study. Subjects may receive other medications as deemed medically necessary by the investigator. It is important for the investigator to review each medication (prescription and non-prescription) received by the subject prior to study entry and at each study visit.

At each visit, subjects must be asked about any new medications they have received since the previous visit;

In order to reduce the risk of drug interactions, all measures must be taken to limit the number of concurrent administrations that are truly necessary;

Drugs that are hepatotoxic (i.e., drugs with warnings of hepatotoxicity in the product insert) should be avoided during administration. Investigators are encouraged to review the potential hepatotoxicity of each drug by searching the [www.livertox.nih.gov](http://www.livertox.nih.gov/) website.

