**Table 8. Treatment Visits Process**

| **Treatment Period** | **Cycle 1**  **D1** | **Cycle 2**  **D1±3** | **N^th^ cycle**  **D1±3** | **Note** |
| --- | --- | --- | --- | --- |
| Laboratory Tests and AE Assessment | X | X | X | All AEs that occur after signing the informed consent form to 30 days after the last dose must be monitored and documented. If a subject starts a new anti-tumor treatment during the AE collection period, then only treatment-related AEs should be collected after the start of new anti-tumor treatment. |
| Concomitant Medications | X | X | X | All concomitant medications/treatments from 28 days prior to study treatment until the end of the safety follow-up period should be collected. If a subject starts a new systemic anti-tumor treatment during the study, then only concomitant medications/treatments used for study treatment-related AEs should be documented. |
| Evaluation of Efficacy | | | | |
| Imaging Evaluation |  | X | X | Refer to section12.3 and 12.4 |
| Infusion of Study Drugs | | | | |
| Camrelizumab | 200mg IV, Q3W | | | Refer to section 8. |
| Apatinib | 250mg PO QD | | | Refer to section 8. |
| Carboplatin | AUC 5 mg/mL/min IV Q3W | | | Refer to section 8. |
| Etopside | 100 mg/m2 IV Day 1-3 Q3W | | | Refer to section 8. |

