## End of Treatment

End of treatment refers to withdrawal from the study. An end-of-treatment visit is required ± 3 days from the time of the decision to terminate treatment and/or withdraw from the study. Refer to Table 9 for the flow chart for end-of treatment visits.

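### Section 10.2 allows palliative bone radiotherapy without the sponsor approval and target-lesion bar that section 10.3 requires, so an irradiated target lesion could count as a response

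*Protocol*

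**What the plan says.** Two parts of section 10 of the protocol govern radiotherapy during treatment.

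- **Section 10.2**, on supportive care, covers bone metastases whose pain persists despite systemic treatment or local pain relief. In that situation, "small-area (radiotherapy area must be <5% bone marrow area) irradiation with palliative radiotherapy is permitted". It does not mention sponsor approval, the number of lesions, or whether the lesion is a target lesion.
- **Section 10.3**, on other anti-tumour treatment, lists radiotherapy among the treatments prohibited during the treatment period. A note gives the only exception, which leaves it to the sponsor's discretion to "approve and allow radiation therapy to symptomatic isolated lesions or to the brain as long as it is not a lung or target lesion". No field limit is given. After the list, the section adds: "Subjects requiring any of the above treatments, as assessed by the investigator, should be excluded from the study".

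Neither section cites the other, and nothing in the protocol says which prevails.

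Section 12.2 defines ORR, DCR, DoR and PFS, with RECIST v1.1 as the response standard. None of the definitions mentions radiotherapy to a measured lesion.

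**The concern.** The two sections answer the same clinical question differently. An investigator with a subject in pain will naturally look in the supportive-care section. That section gives permission subject to one condition and does not point to the stricter rule that follows it.

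Two things are at stake:

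- **Efficacy measurement.** If the painful lesion is a target lesion, its later shrinkage or stability may reflect the radiotherapy and not the study drugs. The lesion would still be measured and would still contribute to ORR, DCR, DoR and PFS. Section 10.3 bars target lesions, but 10.2 does not carry that bar.
- **Compliance.** Radiotherapy given in good faith under 10.2, without approval, is a prohibited treatment under 10.3.

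**Working it through.** The protocol gives no figure for this point, so the check is a comparison of conditions. The subject has a painful bone metastasis that systemic treatment or local analgesia does not control, and the field is below 5% of marrow area.

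| Condition | Section 10.2 | Section 10.3 |
|---|---|---|
| Sponsor approval | not mentioned | required |
| Target lesion | not mentioned | barred |
| Number of lesions | not mentioned | isolated lesions only |
| Field size | below 5% of marrow area | not mentioned |

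Applied to concrete cases:

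1. *One non-target lesion, no approval sought.* Section 10.2 permits it and 10.3 prohibits it.
2. *One target lesion.* Section 10.2 permits it. Section 10.3 prohibits it, and the sponsor has no power under that section to approve it.
3. *Several painful non-target lesions, total field within the limit.* Section 10.2 permits it. The 10.3 exception, read literally, does not reach it.
4. *One isolated non-target lesion, approved.* Both sections permit it.

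Case 2 is the one that matters for analysis. The steps are: 10.2 permits the irradiation; the lesion remains a target lesion; section 12.2 takes best overall response as assessed, with no condition about local treatment; so any response or control in that lesion enters the efficacy results.

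**Scale of one case.** The planned sample is 36 (section 4). If all 36 are dosed and form the denominator, one subject whose best response changes moves ORR or DCR by 1/36 = 0.028, or 2.8 percentage points. This is the weight of a single subject. It does not predict how many subjects are affected, because the protocol gives no frequency of painful bone lesions or of bone lesions chosen as targets.

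**The case against.** The strongest reply is that the sections can be obeyed together. Section 10.2 permits and does not require, so a site that also meets every condition in 10.3 breaches neither. Alternatively, 10.2 can be read as the specific rule for bone pain and 10.3 as the general rule for anti-tumour treatment.

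Both readings are available, but the protocol states neither. The second would allow irradiation of target lesions, which 10.3 expressly rules out. The first works only for a site that knows to look in 10.3.

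Some stronger readings are tempting, and the documents do not support them:

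- **A field of 5% or more as a further conflict.** Section 10.3 gives the sponsor discretion and gives no right to a larger field, so applying the 5% cap breaches nothing.
- **Approved radiotherapy leading to exclusion.** A reader might infer this from "Subjects requiring any of the above treatments, as assessed by the investigator, should be excluded from the study". The same list contains expressly allowed uses, such as corticosteroids for immune-related events. The sensible reading is that the sentence covers prohibited uses only.
- **A removal ground missing from sections 6 and 8.** Section 6 includes "Other situations where the investigator felt it necessary to withdraw from the study", and section 8 allows discontinuation on the investigator's evaluation. Since 10.3 also leaves the matter to the investigator's assessment, there is no gap.
- **Loss of primary safety data.** Table 8 narrows adverse-event collection after a new anti-tumour treatment starts. No text says palliative radiotherapy is such a treatment, and 10.2 places it under symptom care.

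**Conclusion.** The point holds in a limited form. Sections 10.2 and 10.3 differ on sponsor approval and on target lesions. Followed as written, 10.2 allows a target bone lesion to be irradiated with its response still counted, and allows radiotherapy that 10.3 forbids.

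The impact is minor. Safety is the primary endpoint, efficacy is secondary and descriptive, and only two centres are named. The effect on ORR, DCR, DoR or PFS cannot be estimated from the documents.

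The conclusion assumes that at least some bone lesions could be selected as target lesions; nothing in the protocol prevents this. It does not depend on what a statistical analysis plan might say about handling irradiated lesions, because the conflict lies in what treatment is permitted.

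**What to change.** Make three short changes:

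1. In section 10.2, after the field limit, add: *non-target lesions only, with sponsor approval as in section 10.3*.
2. In the radiotherapy item of section 10.3, name this use as an exception, and say that it includes more than one painful bone lesion provided the total field stays below 5% of marrow area.
3. State that subjects irradiated under this exception remain on study.

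The isolated-lesion condition should not be carried into 10.2. It would deny palliation to subjects with several painful bone lesions, and the target-lesion bar already protects the measured lesions.

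The drafting cost is two or three sentences in one amendment. There are two clinical costs: approval may delay pain relief slightly, and a subject whose painful lesion is a target lesion could not have it irradiated while on study treatment. The second is already the position under 10.3, but it should be accepted knowingly.
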